### Laboratory tests

Blood samples will be collected and centrifuged within 10 min. The supernatant fluid will be pipetted and stored in a cryotube at −80 °C in Beijing Hospital of Traditional Chinese Medicine, Capital Medical University. The levels of hepatic and renal function indicators, routine blood and urine tests will be assessed at the Clinical Laboratory in the same hospital. The cryopreserved supernatant fluid will be tested via an enzyme-linked immunosorbent assay (ELISA) kit or chemical kit within 6 months to assess the serum levels of SOD and MDA. The instruments used during testing include an electronic balance (YP30001, Shanghai Guangzheng Medical Instruments Co., Ltd., China), a mini-shaker [MS1 Minishaker, IKA (Guangzhou) Instruments and Equipment Co., Ltd., China], a desktop low-speed automatic-balancing centrifuge (LDZ5- 2, Beijing Jingli Centrifuge Co., Ltd., China), an electric constant-temperature water tank (HW. W21.600, Beijing Changfeng Instrument and Meter Company, China), and a multifunction microplate reader [SpectraMax M2, Meigu Molecular (Shanghai) Instruments Co., Ltd., China].

### Data collection and management

Data for each participant will be recorded in a case report form. Patients are required to attend the assessment every 14 days and finish the trial with 5 evaluations, including the enrollment evaluation (0 days, 14 ± 2 days, 28 ± 5 days, 42 ± 5 days, and 56 ± 5 days). Each evaluation included general demography, relevant medical history and diagnosis, safety evaluation, blood pressure assessment in the consultation room, symptom improvement assessment, target organ damage assessment, cardiovascular risk factor assessment, and other methods, such as adverse event recording, combined drug recording, and compliance assessment, as shown in Figure 2. Baseline blood pressure will be measured using standardized procedures, and the average of at least two measurements will be recorded for each participant.

**Figure 2 F2:**
[figure not shown]
Schedule of enrollment, interventions, and assessments.

Data management will be performed by two researchers through a website completely independent of the investigators and the sponsor. The system, which will be protected by passwords, will be managed by Beijing Cardiar Technology Co., Ltd. (Unified Social Credit Identifier 91110 10,655 68,170 240). All data supporting the conclusions of this trial will be stored in this system. To ensure data integrity and ease of storage, we use data rules, valid values, and scope checks. The system reports missing data and data errors. The data may be changed, but all changes will be tracked. The trial will be audited by Beijing Inruida Pharmaceutical Technology Co., Ltd. (Unified Social Credit Identifier 91110105MA00H1U54L). These data management procedures will be undertaken completely independently of the investigators and the sponsor. All the data management, including coding, storage, security, and cleaning, will be performed according to the data rules, valid values, and scope checks. The conduct of the trial will be audited through a website (http://www.cardiar.com/zryygxy). The personal information of all participants will be fully protected. The original case report forms will be kept for 5 years after the end of the trial.

### Adverse events

The study is largely a low-risk exploratory trial. However, any signs of adverse event symptoms that occurred during the observation period were required to inform the study nurse immediately and be recorded in the case report. Common adverse events (AEs) include gastrointestinal reactions such as malignant, abdominal distension, abdominal pain, skin reactions such as facial flushing, skin rash and mild cough. AEs should be reported to the research leader, sponsor, and ethics committee within 24 h by the clinical researcher for further treatment decisions. An AE will be categorized as related (definitely, probably, or possibly) or not related (unlikely or not related) to the study drug. An adverse drug reaction (ADR) will be defined as an AE that is considered related to the study drug.

### Statistical analysis

#### Sample size calculation

The sample size calculation was based on clinical research literature and preliminary clinical data. On the basis of the design of the superiority test, we assume that the efficiency of the placebo group is approximately 30%, and the efficiency of the experimental group is approximately 65%. In accordance with the statistical superiority test (superiority threshold of 0), *α* takes a unilateral value of 0.025. When the grouping ratio was 1:1 under the condition of 80% certainty, the control group and the experimental group needed 27 cases each as the evaluable number of cases. Considering the length of the district group and the 20% shedding rate, 36 patients were planned to be enrolled in each group, and a total of 72 patients were needed. PASS11 software was used to calculate the sample size.

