#### Data analysis

SPSS 15.0 (PN: 32119001, SN: 5045602) will be used for statistical analysis. The measurement data are expressed as the means ± standard deviations. Between-group comparisons of two groups of normally distributed and variance-aligned continuous variables were performed via t tests. Comparisons between groups of two normally distributed continuous variables with chi-square variance between each stratum will be performed via analysis of variance (ANOVA) with randomized area group design data, and two-by-two comparisons between multiple groups will be performed via the SNK-q test. Comparisons between groups of nonnormally distributed continuous variables will be performed via the rank sum test. Comparisons between groups of count data were performed via the chi-square test, and Fisher's exact probability test will be used when the expected frequency is <5. Major adverse cardiac events will be evaluated via Cox regression analysis. *P* < 0.05 is considered a statistically significant difference. Baseline blood pressure levels will be included as covariates in the statistical analysis to minimize potential confounding effects.

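### 27 evaluable patients per arm do not give 80% power with the chi-square test the protocol names: power is about 72–74%, and 31 per arm are needed

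*Protocol article*

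**What the plan says.** The Sample size calculation section of the protocol article fixes every input. For the response rates, "we assume that the efficiency of the placebo group is approximately 30" per cent and "the efficiency of the experimental group is approximately 65" per cent. The test is for superiority with a "superiority threshold of 0", and alpha "takes a unilateral value of 0.025". Allocation and power are given by "When the grouping ratio was 1:1 under the condition of 80% certainty". The result is that "the control group and the experimental group needed 27 cases each as the evaluable number of cases". After allowing for block length and "the 20% shedding rate, 36 patients were planned to be enrolled in each group", the total is 72. The software is named (PASS 11), but the test option used in it is not.

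The Data analysis section says "Comparisons between groups of count data were performed via the chi-square test", with Fisher's exact test reserved for expected frequencies below 5. It also says baseline blood pressure will be a covariate, without naming a model for a binary outcome.

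**The concern.** The primary endpoint is a responder proportion, so the chi-square rule in the Data analysis section applies to it. The standard two-proportion formula for that test does not return 27 from the protocol's own inputs. The calculation is the only justification given for the trial's size. If the 80% is not a property of the planned comparison, a non-significant result would be read as stronger evidence against the assumed 35-point effect than it is.

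**Working it through.** **Inputs, all from the Sample size calculation section.** p₁ = 0.30, p₂ = 0.65, difference 0.35, margin 0, one-sided alpha 0.025 (z = 1.960), power 80% (z = 0.8416), 1:1 allocation. The mean rate is (0.30 + 0.65)/2 = 0.475. The variance terms are 0.30 × 0.70 = 0.21 and 0.65 × 0.35 = 0.2275, which sum to 0.4375.

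**Which test applies.** At 27 per arm the expected counts are 27 × 0.475 = 12.8 responders and 27 × 0.525 = 14.2 non-responders. Both are well above 5, so the protocol's rule selects chi-square, not Fisher.

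**Reproducing 27.** Closed formulas, per arm:

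- Pooled (chi-square): [1.960 × √(2 × 0.475 × 0.525) + 0.8416 × √0.4375]² / 0.35² = (1.3842 + 0.5567)² / 0.1225 = 3.767 / 0.1225 = 30.75, so 31.
- Arcsine: 30.60, so 31.
- Unpooled variance: (1.960 + 0.8416)² × 0.4375 / 0.1225 = 28.03, so 29.
- Continuity-corrected: 36.24, so 37.
- One-sided alpha 0.05 instead of 0.025: pooled 25, unpooled 23, continuity-corrected 30.

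None gives 27. The one route found that does is exact binomial enumeration of the unpooled Z test: 78.2% power at 26 and 80.6% at 27.

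**Power at 27 with the named test.** Normal approximation: Φ[(0.35 × √27 − 1.3842) / √0.4375] = Φ(0.657) = 74.4%. Exact enumeration: 72.4%.

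**Power by evaluable number per arm**

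| n per arm | Chi-square, approximate | Chi-square, exact | Unpooled Z, exact |
|---|---|---|---|
| 27 | 74.4% | 72.4% | 80.6% |
| 28 | 76.0% | 75.1% | 77.2% |
| 29 | 77.5% | 77.4% | 78.0% |
| 30 | 79.0% | 79.8% | 79.9% |
| 31 | 80.3% | 81.9% | 82.0% |
| 36 | 86.0% | 85.2% | 86.3% |

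The 80.6% for the unpooled test is a local peak caused by discreteness. Its exact power falls below 80% at 28 and does not return there until 31.

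**Type I error at 27.** The maximum one-sided error over common response rates is 0.0380 for the unpooled Z test and 0.0285 for chi-square. Both exceed 0.025, the unpooled test by far more. Boschloo's test, which does hold 0.025, has 72.0% power at 27, close to the chi-square figure.

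**Effect of loss.** 27/0.8 = 33.75, so 36 per arm covers a requirement of 27. But 36 × 0.8 = 28.8 is short of 31. The loss that still leaves 31 is 1 − 31/36 = 13.9%. To have 31 after 20% loss, 31/0.8 = 38.75, so 39 per arm, or 78 in total.

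**The case against.** The strongest reply is that nothing was miscalculated. An unpooled Z test with exact enumeration yields 27, and the protocol does not say which option was used in the software. That is fair as to the label: this is better described as a mismatch between the test used for sizing and the test planned for analysis than as a slip of arithmetic. It does not rescue the sentence. That test is not the one named for analysis, its error rate is well above the stated alpha, and its advantage vanishes at the 28 to 29 per arm the protocol expects to keep.

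Second, the chi-square rule is generic, and the covariate sentence hints at an adjusted model that may be set out elsewhere. This is a real ambiguity, but the sample size section claims no gain from adjustment, so it cannot support 27.

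Third, the practical shortfall is modest. With 36 enrolled, power at the assumed loss is 75–78%, not 72–74%. The rates are stated as approximate: by the pooled formula, a true experimental rate of 67.5% would restore 80% at 27. This stands, and it limits the consequence.

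Fourth, the trial is called exploratory, and its Limitations section concedes limited power. That concession concerns subtle effects, however, not the large difference assumed, and the formal 80% claim remains in the text.

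**Conclusion.** The concern holds. With the protocol's own inputs and the chi-square test it names, 27 evaluable per arm gives about 72–74% power, and 31 are needed for 80%. At the protocol's assumed 20% loss, the chance of missing the assumed effect is about 22–25% rather than 20%. If all 36 per arm are analysed, power is 85–86% and the target is exceeded. The conclusion rests on chi-square, without continuity correction, being the primary analysis, which is the natural reading of the Data analysis section. The deficit is moderate, but the stated figure is wrong for the design as described.

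**What to change.** Keep 72 patients and correct the Sample size calculation section, for example:

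> With the chi-square test at one-sided 0.025, 31 evaluable patients per arm are needed for 80% power to detect 30% versus 65%. Enrolling 36 per arm gives about 86% power with no loss, at least 80% with loss up to 14%, and about 76% with 20% loss.

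Name the test used in the calculation, and state that the same test is the primary analysis of the responder endpoint. If an adjusted model is intended instead, say so and give the power on that basis.

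The cost is wording only, with no extra patients. The correction openly gives up 80% power at the assumed 20% loss. If that target is to be kept, enrolment would have to rise to 39 per arm (78 in total, 6 more than planned), which is still possible to decide because the Trial status section reports 40 recruited.

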#### Data analysis

SPSS 15.0 (PN: 32119001, SN: 5045602) will be used for statistical analysis. The measurement data are expressed as the means ± standard deviations. Between-group comparisons of two groups of normally distributed and variance-aligned continuous variables were performed via t tests. Comparisons between groups of two normally distributed continuous variables with chi-square variance between each stratum will be performed via analysis of variance (ANOVA) with randomized area group design data, and two-by-two comparisons between multiple groups will be performed via the SNK-q test. Comparisons between groups of nonnormally distributed continuous variables will be performed via the rank sum test. Comparisons between groups of count data were performed via the chi-square test, and Fisher's exact probability test will be used when the expected frequency is <5. Major adverse cardiac events will be evaluated via Cox regression analysis. *P* < 0.05 is considered a statistically significant difference. Baseline blood pressure levels will be included as covariates in the statistical analysis to minimize potential confounding effects.

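### Baseline blood pressure is promised as a covariate, but no model that can take a covariate is named for the primary or the continuous endpoints

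*Protocol article*

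**What the plan says.** The Data analysis section of the protocol article assigns a method to each type of outcome:

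- Normal continuous variables with equal variances: "Between-group comparisons of two groups of normally distributed and variance-aligned continuous variables were performed via t tests".
- A further case, described through strata: "analysis of variance (ANOVA) with randomized area group design data", after which "two-by-two comparisons between multiple groups will be performed via the SNK-q test".
- Non-normal continuous variables: "Comparisons between groups of nonnormally distributed continuous variables will be performed via the rank sum test".
- Counts: "Comparisons between groups of count data were performed via the chi-square test, and Fisher's exact probability test will be used" when an expected frequency falls below 5.
- Cardiovascular events: "Major adverse cardiac events will be evaluated via Cox regression analysis".

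The paragraph then closes with "Baseline blood pressure levels will be included as covariates in the statistical analysis to minimize potential confounding effects". That sentence names neither an endpoint nor a model.

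The Primary endpoint section defines a between-group difference in the proportion of responders, so the primary comparison comes under the rule for counts. The Design and Randomization sections give two arms at 1:1.

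**The concern.** A covariate needs a model to sit in. Of the methods listed, the chi-square, Fisher, t and rank-sum tests have no place for one. The section thus commits to an adjustment that its own tests for the primary and continuous endpoints cannot perform.

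Two primary results are possible, one unadjusted and one adjusted for baseline blood pressure, and this text does not say which decides. With 36 patients per arm some chance baseline imbalance is to be expected, and the two results could fall on opposite sides of P < 0.05.

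For continuous outcomes the tests named also give up precision that baseline values already being collected would provide. For HbA1c, lipids, pulse wave velocity and the oxidative stress markers, the useful covariate is the outcome's own baseline rather than blood pressure.

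**Working it through.** **1. The plan's own sample size.** Inputs from Sample size calculation: response 30% and 65%, one-sided alpha 0.025, power 80%, 1:1, margin 0. The unpooled formula is n = (1.960 + 0.842)² × (0.30×0.70 + 0.65×0.35) / 0.35² = 28.03, rounded up to 29 per arm. The plan states 27, where the same formula gives 78.5% power. This is within two patients of the plan's figure. The pooled formula gives 31. The present point does not depend on the difference. What matters is that the trial was sized by an unadjusted comparison of two proportions.

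**2. Which test the plan's rule selects for the primary endpoint.** At 27 per arm the pooled response rate is (0.30 + 0.65)/2 = 0.475. The expected cells are 27 × 0.475 = 12.8 and 27 × 0.525 = 14.2. Both exceed 5, so the rule leads to the chi-square test, which is unadjusted.

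**3. Methods against the covariate promise.**

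| Outcome | Method named | Takes a covariate? |
|---|---|---|
| Primary responder rate | Chi-square or Fisher | No |
| Continuous, normal | t test | No |
| Continuous, non-normal | Rank sum | No |
| Cardiovascular events | Cox regression | Yes |

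The block ANOVA as named carries a block factor, not a baseline covariate.

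**4. Room for chance imbalance.** In standard deviation units, the standard error of a baseline mean difference at 36 per arm is √(2/36) = 0.24.

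**5. Cost for continuous outcomes.** Assumption: the correlation ρ between baseline and week 8 is 0.5 to 0.7; the document gives no value. Variance relative to ANCOVA:

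- Week-8 values only: 1/(1 − ρ²) = 1/0.75 = 1.33 at ρ = 0.5, and 1/0.51 = 1.96 at ρ = 0.7.
- Change scores: 2(1 − ρ)/(1 − ρ²) = 1.00/0.75 = 1.33 at ρ = 0.5, and 0.60/0.51 = 1.18 at ρ = 0.7.

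At ρ = 0.5, moving from either t test to ANCOVA is worth about one third more patients.

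**6. SNK-q with two groups.** With 2 × 27 − 2 = 52 degrees of freedom, the SNK critical value q/√2 is 2.0066 and the t critical value is 2.0066. The procedure reduces to the t test.

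**7. How large a primary model the data can carry.** Expected responders at 27 per arm: 27 × 0.30 + 27 × 0.65 = 8.1 + 17.55 = 25.65, about 26. Arm plus baseline SBP leaves 25.65/2 = 12.8 responders per coefficient. One further covariate leaves 25.65/3 = 8.6. Five coefficients (arm, SBP, DBP, HbA1c, glycaemic category) would leave 25.65/5 = 5.1, which is too few, and SBP and DBP are correlated as well.

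**The case against.** The best defence is that this is a condensed article. The form of an adjusted model is commonly left to a statistical analysis plan, which is not shown and may settle the matter. That stands as far as it goes: it is not shown that the choice of primary analysis will be made after the data are seen. But the article is not silent on method. It names tests and then states something those tests cannot do, and that mismatch is on the page whatever another document says.

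Several stronger readings are tempting and are not supported:

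- A reader might infer that the covariate sentence cannot be carried out at all. Cox regression accepts covariates, so it can be carried out for cardiovascular events.
- A reader might infer that a block ANOVA is unfit for a two-arm parallel trial. The Sample size calculation section contains a phrase that reads as a mistranslated block length. Moreover, 27/0.8 = 33.75, so 34 per arm would cover dropout, and the planned 36 is consistent with rounding up to complete blocks. If randomisation was blocked, a treatment-plus-block ANOVA is valid with two arms. The fair complaint is that the sentence is garbled and defines no strata or blocks.
- A reader might infer that SNK-q will be run across the five visits as if they were independent samples. Nothing in the document says so, and the Design section describes efficacy assessment before and after 8 weeks.
- A reader might carry the variance ratios over to the primary endpoint. They are linear-model results for continuous outcomes and say nothing about a binary response.

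**Conclusion.** The inconsistency is real and lies within one paragraph. For the primary endpoint and all continuous endpoints, the promised adjustment cannot be made with the tests named, and this text leaves open whether the primary result is adjusted. No size is claimed for the primary endpoint. An unadjusted chi-square test is itself a valid comparison in a randomised trial; the fault is the ambiguity.

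For continuous outcomes the loss against ANCOVA is 33% to 96% in variance if week-8 values are compared, and 18% to 33% if change scores are. Both ranges rest on the assumed correlation of 0.5 to 0.7, and the document does not say which of the two the t tests will use. SNK-q is superfluous but harmless between two arms. The point should be corrected, but it does not threaten the trial's validity.

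**What to change.** Rewrite the paragraph before unblinding:

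- **Primary endpoint.** Name one analysis. Either fit a logistic model of response on arm and baseline SBP, with at most one further prognostic covariate fixed in advance, reporting a standardised risk difference with 95% CI and the chi-square test as sensitivity. Or keep the chi-square test as primary and label the adjusted model as sensitivity.
- **Continuous outcomes.** Use ANCOVA of the week-8 value on arm and that outcome's own baseline, with any transformation fixed in advance.
- **Cardiovascular events.** State whether the covariate promise applies to the Cox model.
- **Remaining sentence.** Remove SNK-q. Keep a block term only if randomisation was blocked, and then define the blocks.

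The cost is the wording of one paragraph. Baseline blood pressure and the baseline values of the continuous outcomes are already part of the assessments, so no new data are needed. The Trial status section reports 40 patients recruited and completion by June 2026, so there is time if the blind is intact.

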## Discussion

The coexistence of hyperglycemia and hypertension represents a critical synergistic risk factor for CVD, substantially elevating both morbidity and mortality (25). Early and effective intervention in this high-risk population is therefore essential to attenuate the progression of atherosclerotic cardiovascular disease (ASCVD), improve long-term outcomes, and alleviate the growing burden of chronic disease management (26). Despite the clear clinical significance, there remains a notable gap in robust therapeutic strategies specifically targeting the confluence of glucose metabolism disorders and hypertension (27).

YQSJ represents a traditional Chinese medicine formulation with over three decades of clinical application in the management of metabolic disorders at a leading tertiary hospital. Preclinical pharmacological investigations suggest that its bioactive components may exert hypoglycemic and antihypertensive effects through modulation of the IRS-1/PI3K/AKT signaling pathway, a key regulator of metabolic and vascular homeostasis (13).

While prior research has primarily examined the efficacy of YQSJ in prediabetic populations, high-quality clinical evidence regarding its utility in patients with concurrent hypertension and abnormal glucose metabolism is lacking. This protocol outlines a randomized, double-blind, placebo-controlled trial designed to evaluate the blood pressure-regulating effect of YQSJ in this specific patient cohort. Beyond assessing conventional endpoints such as blood pressure and glycemic parameters, this study will incorporate a comprehensive evaluation of cardiovascular risk profiles, including lipid metrics, the triglyceride-glucose index, vascular function, and patient-reported health outcomes. An embedded health-economic analysis will further assess the cost-effectiveness of the intervention.

Looking ahead, planned multi-omics analyses of collected biological samples aim to elucidate the systemic mechanisms underlying the therapeutic effects of YQSJ, bridging clinical observations with molecular insights. We anticipate that this trial will contribute empirical evidence supporting the integration of TCM-based approaches into outpatient management pathways for this high-risk population.

